
## 2 Background and rationale

### ILC

Invasive lobular breast cancer (ILC) is the most frequent special histological subtype of breast cancer (5-15%) after invasive breast carcinoma of no special type (NST) previously known as invasive ductal breast cancer (IDC). [27] ILC is typically characterized by non-cohesive cells individually dispersed or arranged in a single-file linear pattern in fibrous stroma. ILCs mostly express the estrogen receptor (ER), lack HER2 and lost the cell adhesion molecule E-cadherin. Several special ILC subtype have been described on the basis of architecture (solid, alveolar), cytonuclear characteristics (pleomorphic, tubulolobular) and a mixed non-classical is composed of cases showing an admixture of the classic type with one or more of these variant patterns. [28] The classic ILC and mixed variants contribute to the majority of ILCs comprising up to 75% of all cases. In addition, both invasive carcinoma NST and lobular features of differentiation are present in about 5% of invasive breast cancers.

ILC has a distinctive biology and clinical behavior compared with IDC. For example, the prognostic impact of histology (ILC vs IDC) appears to vary with time. This was shown in a pooled analysis of over 9000 patients with extended follow-up that reported a 16 percent lower risk of recurrence for ILC compared with IDC during the first six years of follow-up; however, ILC conferred a 54 percent higher risk of relapse after six years. [29] For metastatic ILC patients who are refractory to endocrine treatment, no first or second line 'standard' therapies have been defined. Frequently used anticancer agents are capecitabine, or a taxane. The median progression-free survival (PFS) reached with these therapies typically lies between 2-4 months only, but limited data are available. [25, 26] In conclusion, there is a clear clinical need for new treatment options for patients with metastatic ILC.

### Immune checkpoint inhibitors in breast cancer

No data are available regarding response to checkpoint blockade in ILCs. However, preliminary data of early immunotherapy trials in ER-positive breast cancer show a modest response rate to anti-PD(L)1 monotherapy: 2.8% (n=72, including 6 ILCs) with anti-PD-L1 monotherapy in ER-positive breast cancer not selected for PD-L1 positivity. [6] The response rate increases to 12% (n=25, number of ILCs unknown) in the PD-L1 positive ER-positive breast cancers [7] with a clinical benefit rate (defined as objective response or stable disease for over 24 weeks) of 20%. Although the sample size is small and the patients were heavily pretreated, the response rate in ER-positive breast cancer seems lower compared to other breast cancer subtypes such as triple negative breast cancer (TNBC) with response rates between 10-20%. [6, 30-32] This illustrates the need for the discovery of predictive biomarkers that can aid in selecting breast cancer patients for immunotherapy. Moreover, the challenge lies ahead of us to combine anti-PD(L)1 with novel immune-modulatory drugs or conventional anti-cancer treatments that are able to increase the immunogenicity of breast tumors.

### Gene expression: immune-related ILC subtype

Besides its tendency to relapse later in the disease course, ILCs are more likely to metastasize to the bone, peritoneum, gastrointestinal tract and ovaries suggesting a different underlying biology. [33] Recently, three independent groups presented a comprehensive molecular characterization of ILCs. [8-10] Investigators from our institute performed a large-scale genomic analysis of ILCs and identified an immune related (IR) subtype within ILCs characterized by mRNA up-regulation of CD4, CD8, PD-L1, PD1 and CTLA4 and greater sensitivity to DNA-damaging agents. [9] Tumor with this immune-related gene signature show significantly

more lymphocytic infiltration. In line with this, researchers from The Cancer Genome Atlas (TCGA) have shown that immune-related genes (interleukins, chemokines, MHC complex, IDO1 and IFN $\gamma$ ) are highly expressed in a subset of ILC tumors. [10] This molecular characterization may help select ILC patients for immunotherapy in the future.

#### Exploiting the immune-modulatory effect of chemotherapy

Since classical anticancer agents can stimulate immune effector cells [11, 12], we hypothesize that induction treatment with chemotherapy induces an anticancer immune response resulting in synergistic activity with anti-PD-L1. Another benefit of adding chemotherapy to immunotherapy could be that the cytostatic effect of chemotherapy provides relatively rapid tumor control in the window of several weeks before the response to anti-PD(L)1 occurs. The first data on chemotherapy plus anti-PD-L1 show that the response rates are indeed higher when anti-PD-L1 is administered in combination with chemotherapy. [30] In this trial, we will use carboplatin as immune response induction treatment. Carboplatin not only stimulates class I HLA expression but also inhibits signal transducer and activator of transcription 6 (STAT6)-regulated expression of programmed death ligand 2 (PD-L2), thus limiting immunosuppression by both dendritic cells (DCs) and tumor cells. [13] And work of the Melief group showed that low dose platinum and vaccination act synergistically in tumor eradication. [14] In addition, preliminary work in a mouse model for ILC [15] performed by the [name] lab at our institute suggests that the activity of T-cell check point inhibitors is enhanced using platinum agents (work in progress). Moreover, the fact that cell lines of the IR subtype show greater sensitivity to DNA-damaging agents [9] provides additional evidence to combine PD-1-blockade with carboplatin in this GELATO-trial.

#### **Rationale**

Eventually all patients with metastatic ILC will become resistant to endocrine treatment and no targeted therapies are currently available for this subgroup. Recently, two independent research consortia have identified a subgroup of ILC that harbor upregulation of immune-related genes including IFN $\gamma$ , type I IFNs, MHC and chemokines as well as PD-1, PD-L1 and CTLA-4. This so called immune-related (IR) subtype of ILC shows a greater sensitivity to DNA-damaging agents in vitro and in a mouse model for ILC a synergy between checkpoint-blockade and platinum is observed. Therefore, we hypothesize that anti-PD-L1 in combination with platinum could be effective in ILC. More specific, we will explore whether this effect is more pronounced in the subgroup of ILC with an IR signature.

## 3 Objectives and endpoints

### 3.1 Primary Objective

To assess the efficacy of atezolizumab in combination with carboplatin in metastatic ILC

### 3.2 Secondary Objective

- To evaluate the outcome after atezolizumab together with carboplatin in the IR-profile subgroup vs the non-IR-subgroup as defined by gene expression profiling (retrospectively defined as previously described [9])
- To evaluate the safety of atezolizumab together with carboplatin
- To evaluate the efficacy of atezolizumab plus carboplatin using objective response rate
- To evaluate the efficacy of atezolizumab plus carboplatin using proportion of patients free of progression at 12 months
- To evaluate the efficacy of atezolizumab plus carboplatin using overall survival
- To explore the role of potential biomarkers to predict response to atezolizumab plus carboplatin

### 3.3 Translational studies

- Analyze the increase in immunogenicity after immune response induction treatment using carboplatin using pre-treatment biopsies/blood samples and biopsies/blood samples taken after 2 cycles of carboplatin before the start of atezolizumab. Potential markers to assess immunogenicity: TILs, PD-L1, CD8, FOXP3, CD68 (IHC), changes in gene expression with an emphasize on IFN $\gamma$ -related gene signatures [18, 19], serum cytokine levels, proportion of effector T cells and myeloid subpopulations in peripheral blood [20] (in collaboration with [name] and the [name] labs)
- Comprehensive analyses of responding and non-responding cases using potential predictive markers such as but not limited to TILs, PD-L1 (according to the algorithm of Roche diagnostics), CD8, CD68, number of neoantigens, IFN $\gamma$ -related gene signatures and serum LDH
- Biobanking of tumor tissues (frozen and FFPE), serum, plasma, whole blood and stool samples. All collected at baseline, after induction/before start atezolizumab (cycle 1), before third, fifth and seventh cycle of atezolizumab (cycle 3, 5 and 7) for the purpose of retrospective analyses of candidate biomarkers or experiments to gain insight into response to immunotherapy in ILCs.

### 3.4 Endpoints

The primary endpoint is:

Proportion of patients who remain free of progression at 6 months. Progression as defined by RECIST 1.1 [34] will be used.

The secondary endpoints are:

- Proportion of patients free of progression (RECIST 1.1[34]) at 6 months in the IR-profile subgroup vs the non-IR-subgroup as defined by gene expression profiling(retrospectively defined as previously described [9])
- Proportion of patients who remain free of progression at 12 months. Progression as defined by RECIST 1.1 [34] will be used.
- Progression as defined by iRECIST [17]
- Overall survival

- Percentage of patients with toxicity (according to CTCAE v4.03, Appendix A) and immune-related toxicity defined as the Adverse Events of Special Interest (AESI's) for atezolizumab (see section 6 and Investigator's Brochure for atezolizumab)
- Objective response rate (RECIST 1.1[34])

*The exploratory endpoints are listed in Section 10 Translational Research*

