### 6.1.2 Atezolizumab – Immune-mediated Adverse Events

Given the mechanism of action of atezolizumab, events associated with inflammation and/or immune-mediated AEs have been closely monitored during the atezolizumab clinical program. These include potential dermatologic, hepatic, endocrine, and respiratory events as well as events of hepatitis/elevated liver function tests (LFTs) and influenza like illness that are considered potential adverse drug reactions associated with atezolizumab.

The Adverse Events of Special Interest for atezolizumab are:

- ◆ Pneumonitis
- ◆ Hypoxemia
- ◆ Colitis
- ◆ Endocrinopathies: diabetes mellitus, pancreatitis, adrenal insufficiency, hypo- or hyperthyroidism
- ◆ Vasculitis
- ◆ Hepatitis
- ◆ Transaminitis: Grade  $\geq 2$ , (AST or ALT  $> 3\times$  ULN and bilirubin  $> 2\times$  ULN) or AST/ALT  $> 10\times$  ULN
- ◆ Systemic Lupus Erythromatosus
- ◆ Guillain Barre Syndrome
- ◆ Skin reactions: vitiligo, pemphigus
- ◆ Events suggestive of hypersensitivity, cytokine release, influenza like illness, SIRS, or infusion reaction syndromes

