### 6.3.1.3 Dermatologic toxicity

Treatment-emergent rash has been associated with atezolizumab. The majority of cases of rash were mild in severity and self-limited, with or without pruritus. A dermatologist should evaluate persistent and/or severe rash or pruritus. A tissue sample should be collected for biopsy unless contraindicated.

Dermatologic toxicity and rash should be managed according to the guidelines in Table 3.

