### 6.3.1.4 Endocrine toxicity

Thyroid disorders, hypophysitis and adrenal insufficiency have been associated with the administration of atezolizumab. Patients with unexplained symptoms such as fatigue, myalgias, impotence, mental status changes, or constipation should be investigated for the presence of thyroid, pituitary, or adrenal endocrinopathies, as well as for hyponatremia or hyperkalemia. An endocrinologist should be consulted if an endocrinopathy is suspected. TSH and free T4 levels should be obtained to determine whether thyroid abnormalities are present. TSH, prolactin, and a morning cortisol level will help to differentiate primary adrenal insufficiency from primary pituitary insufficiency. Endocrine toxicity should be managed according to the guidelines in Table 4.

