### 6.3.1.9 Neurologic Disorders

Myasthenia gravis and Guillain-Barre syndrome have been observed with single agent atezolizumab. Patients may present with signs and symptoms of sensory and/or motor neuropathy. Diagnostic work-up is essential for an accurate characterization to differentiate between alternate etiologies. Neurotoxicity should be managed according to the guidelines in Table 8.

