### 6.3.1.11 Immune-related myositis

Myositis or inflammatory myopathies are a group of disorders sharing the common feature of inflammatory muscle injury. Initial diagnosis is based on clinical (muscle weakness, muscle pain, skin rash in dermatomyositis), biochemical (serum creatine-kinase increase), and imaging (electromyography/MRI) features, and is confirmed with a muscle-biopsy. See table 10 for management guidelines of immune-related myositis.

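### The endpoint for immune-related toxicity rests on an AESI list that does not match the immune-mediated toxicities in section 6.3.1 and sets no attribution condition for its non-specific terms

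*Protocol*

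**What the plan says.** The secondary endpoints in section 3.4 include the percentage of patients with CTCAE toxicity and with "immune-related toxicity defined as the Adverse Events of Special Interest (AESI's) for atezolizumab". A pointer follows: "see section 6 and Investigator's Brochure for atezolizumab". The synopsis gives the same definition without the pointer.

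Section 6 contains one AESI list, in 6.1.2, introduced by "The Adverse Events of Special Interest for atezolizumab are" and worded as complete. Its skin entry is "Skin reactions: vitiligo, pemphigus". Its endocrine entry covers diabetes, pancreatitis, adrenal insufficiency and thyroid under- or overactivity. Its only neurological entry is Guillain-Barre syndrome. Hypoxemia stands alone as an entry. Another entry takes in events suggestive of hypersensitivity, cytokine release, influenza-like illness, SIRS or infusion reactions.

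Section 6.3.1 then gives guidance on a wider set of toxicities:
- 6.3.1.3: "Treatment-emergent rash has been associated with atezolizumab".
- 6.3.1.4: "Thyroid disorders, hypophysitis and adrenal insufficiency have been associated with the administration of atezolizumab".
- 6.3.1.9: "Myasthenia gravis and Guillain-Barre syndrome have been observed with single agent atezolizumab".
- 6.3.1.11 is headed as immune-related myositis and begins "Myositis or inflammatory myopathies are a group of disorders sharing the common feature of inflammatory muscle injury".
- 6.3.1.7 and Table 7 cover autoimmune uveitis, iritis and episcleritis.

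The safety population in 9.4 is everyone who started carboplatin.

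**The concern.** An endpoint called immune-related toxicity should count the events that the protocol itself treats as immune-related. Read against 6.3.1, the 6.1.2 list leaves some of these out, including events for which the tables require atezolizumab to be held or permanently stopped. It also lets in some events with no stated link to atezolizumab.

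This is the only immune-specific safety endpoint in 3.4, and section 4.2 says atezolizumab had not previously been given with carboplatin AUC 1.5. The list also steers data collection. From section 7.2.3 onward, visits ask for adverse events of grade 2 or higher plus the AESIs, so the visit schedule does not prompt for a grade 1 event that is off the list, although 11.4 asks for all adverse events.

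**Working it through.** The protocol gives no expected rate or precision target for this endpoint, so there is no figure to reproduce. The check is a term-by-term comparison.

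**Step 1: events managed in 6.3.1, compared with the 6.1.2 list**

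| Event | Where and how 6.3.1 treats it | On the 6.1.2 list? |
|---|---|---|
| Myasthenia gravis | Table 8, same row as Guillain-Barre, permanent stop at every grade | No, although Guillain-Barre is |
| Other autoimmune neuropathy | Table 8, hold at grade 2, permanent stop if life-threatening | No |
| Immune-related myositis | Table 10, withheld at grades 2 and 3, permanent stop at grade 4 | No |
| Autoimmune uveitis, iritis, episcleritis | Table 7, hold at grades 3-4 | No |
| Hypophysitis | 6.3.1.4, with panhypopituitarism in Table 4 | Not by name; some cases enter as adrenal insufficiency or hypothyroidism |
| Rash | Table 3, hold at grade 3, permanent stop for life-threatening immune-mediated cases | Not by name; only vitiligo and pemphigus |

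Colitis, hepatitis, pneumonitis, pancreatitis, thyroid disease, adrenal insufficiency and Guillain-Barre appear in both places. Systemic immune activation (6.3.1.8) is largely covered by the SIRS and cytokine-release wording.

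**Step 2: entries with no attribution condition**

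Hypoxemia, hypersensitivity, SIRS and infusion reactions count whatever their cause. Section 6.3.2 foresees hypersensitivity to carboplatin. Two carboplatin doses precede the first atezolizumab dose (section 4.1), and the safety population starts at carboplatin. As written, nothing excludes a carboplatin reaction in a patient who never received atezolizumab.

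**Step 3: what one patient is worth**

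With 40 patients (section 4.1), 1/40 = 2.5 percentage points. The share is slightly smaller if extra patients start carboplatin but never reach atezolizumab.

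**Step 4: illustration of omissions (assumed rates)**

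Let q be the share of patients whose only immune event is off the list. Expected missed patients = 40q, and P(at least one missed) = 1 − (1 − q)^40.

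| q (assumed) | Expected missed | P(at least one) |
|---|---|---|
| 1% | 0.4 | 33% |
| 2.5% | 1 | 64% |
| 5% | 2 | 87% |
| 10% | 4 | 99% |

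**Step 5: illustration of net direction (assumed rates)**

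Let T be the true immune-related rate, m the share of true cases missed, and f the share of the remaining patients wrongly counted. Observed rate = T(1 − m) + (1 − T)f. Take T = 30%:
- m = 50%, f = 0: 0.30 × 0.50 + 0 = 15%.
- m = 0, f = 20%: 0.30 + 0.70 × 0.20 = 44%.

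The observed rate can fall on either side of the true one. The documents give no values for T, m or f.

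**The case against.** **The definition is wider than 6.1.2.** Section 3.4 points to section 6 as a whole, which includes 6.3.1, and to a Brochure that is not available here. Section 11.2 also refers to section 6 for managing AESIs. This stands in part. A reader might infer that a patient with myositis is certain to be scored as free of immune-related toxicity, and the documents do not support that certainty. But 6.1.2 is the only AESI list in section 6 and is worded as complete, and the synopsis has no pointer. A longer Brochure list would leave two competing definitions and would not correct this one.

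**The non-specific terms are known drug effects.** This is largely fair. Section 6.1.2 calls influenza-like illness a potential adverse drug reaction. Sections 6.1.1 and 6.3.1.5 link hypoxia to atezolizumab, and 6.3.1.10 manages infusion reactions. These terms should not be dismissed as non-immune noise. What remains is that no attribution is asked for in a trial that gives a second drug with its own hypersensitivity risk.

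**Rash is a weak example for size.** One might take the roughly 10% frequency in 6.1.1 and conclude that 4 of 40 patients are left out. That frequency is regardless of attribution, 6.3.1.3 says most rash was mild and self-limited, and some of these patients would also have a listed event. The figure cannot be used that way.

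**Nothing is lost from the safety report.** Off-list events still count in overall CTCAE toxicity (3.4, 9.5), and the DLT rules in 4.2 work separately. This is true and limits the point to one secondary rate.

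**Term lists belong in the SAP.** Often they do, but here the protocol itself fixes the definition, and it conflicts with the protocol's own account of immune-mediated toxicity.

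**Conclusion.** The point holds as a mismatch of definition. Four event groups that 6.3.1 manages as immune-related or atezolizumab-associated are absent from the 6.1.2 list: myasthenia gravis, immune-related myositis, other autoimmune neuropathy and autoimmune eye inflammation. Two more, rash and hypophysitis, are absent by name, and hypophysitis is partly captured through other terms. Hypoxemia, hypersensitivity, SIRS and infusion reactions are counted with no attribution condition. The immune-related rate therefore does not measure what it is named for.

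A reader might go further and conclude that the rate is understated, or overstated. The documents support neither, because the two faults work in opposite directions and no event rates are given. The only firm size is about 2.5 points per misclassified patient in 40. The verdict assumes that 6.1.2 is the operative list. If the Brochure carries a different one, the fault becomes an ambiguous definition and still needs correcting. Overall toxicity, the primary endpoint and the sample size are untouched.

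**What to change.** - In 3.4 and the synopsis, define immune-related toxicity by one explicit term list that reconciles 6.1.2 with the immune-mediated categories of 6.3.1 and with the Brochure.
- Count the non-specific terms (hypoxemia, hypersensitivity, SIRS, infusion reactions) only when the investigator attributes them to atezolizumab.
- Record relation separately for each drug on the eCRF. Section 11.4 only prefers that relation be recorded, and to study medication as a whole. A cut at possible or above would filter little, because 11.5 defines possible as a link that appears unlikely but cannot be ruled out. The rule should therefore ask directly for attribution to atezolizumab.
- Prompt for the added terms at visits in the same way as for the AESIs.
- Tabulate the 6.1.2 AESI list separately.

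The cost is one extra table, one extra eCRF field and a longer visit prompt. The reported rate may move in either direction. No dose or management rule changes.

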## 4 Trial design

### 4.1 Trial design

This Dutch multicenter investigator-initiated study is a single-arm phase II trial including a run-in phase I part. The design is presented in Figure 1. After a biopsy from a metastatic lesion, patients can enter the trial and will start with the immune response induction treatment using carboplatin in a weekly schedule. After two weeks a second biopsy will be taken and atezolizumab will be co-administered in a 3-week-schedule.

A Simon's two-stage (minimax) design will be used (see 'Statistics' section for sample size calculation of the two stages).[22] After 22 patients (stage I, including the first 6 patients in the DLT window, see section below) the proportion of patients free of progression will be determined. If there are 2 or fewer patients free of progression at 6 months in these 22 patients, the study will be stopped. For evaluation of efficacy according to the Simon's two-stage design we will use all patients who received at least 1 cycle of atezolizumab (per protocol population).

Although the evaluation of potential predictive gene profiles such as the IR-profile is part of this trial (see secondary and translational endpoints) patients will not be selected for the trial based on a certain gene profile.

Figure 1

[figure not shown]

### Treatment

Carboplatin AUC 1.5 [17], intravenous administration, weekly schedule, maximum 12 administrations (no steroids necessary). After two administrations of carboplatin, atezolizumab (1200 mg flat dose) will be given in a 3-weekly schedule until tumor progression. Carboplatin will be administered before the atezolizumab infusion.

Carboplatin will be given for 12 weeks. If carboplatin has to be discontinued due to toxicity, atezolizumab can be continued as monotherapy.

Atezolizumab will be given until tumor progression or intolerable toxicity. After 12 months of atezolizumab treatment discontinuation is allowed in case of ongoing response or stable disease. At signs of progression after discontinuation of the treatment, atezolizumab can be re-started.

